# Multimodal intervention in 8- to 13-year-old French dyslexic readers: Study protocol for a randomized multicenter controlled crossover trial

**DOI:** 10.1186/s12887-022-03701-8

**Published:** 2022-12-28

**Keywords:** Dyslexia, Multimodal intervention, Underlying cognitive deficits, Randomized crossover clinical trial, Protocol

## Abstract

**Background:**

Developmental dyslexia, a specific and long-lasting learning disorder that prevents children from becoming efficient and fluent readers, has a severe impact on academic learning and behavior and may compromise professional and social development. Most remediation studies are based on the explicit or implicit assumption that dyslexia results from a single cause related to either impaired phonological or visual-attentional processing or impaired cross-modal integration. Yet, recent studies show that dyslexia is multifactorial and that many dyslexics have underlying deficits in several domains. The originality of the current study is to test a remediation approach that trains skills in all three domains using different training methods that are tailored to an individual’s cognitive profile as part of a longitudinal intervention study.

**Methods:**

This multicenter randomized crossover study will be conducted in three phases and will involve 120 dyslexic children between the ages of 8 and 13 years. The first phase serves as within-subject baseline period that lasts for 2 months. In this phase, all children undergo weekly speech-language therapy sessions without additional training at home (business-as-usual). During the second phase, all dyslexics receive three types of intensive interventions that last 2 month each: Phonological, visual-attentional, and cross-modal. The order of the first two interventions (phonological and visual-attentional) is swapped in two randomly assigned groups of 60 dyslexics each. This allows one to test the efficacy and additivity of each intervention (against baseline) and find out whether the order of delivery matters. During the third phase, the follow-up period, the intensive interventions are stopped, and all dyslexics will be tested after 2 months. Implementation fidelity will be assessed from the user data of the computerized intervention program and an “intention-to-treat” analysis will be performed on the children who quit the trial before the end.

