#### Exclusion criteria (or study exit criteria)

Participants are temporarily or permanently excluded from the study if:They interrupt daily training for more than a continuous period of 15 days without a valid reason determined at the investigator’s discretion.They do not participate regularly in daily training, as left to the investigator’s appreciation.The participants or their parents withdraw their consent.

The interruption may occur after consent has been obtained or after randomization. A child who wishes to withdraw consent may tell his/her parents or the speech-language pathologist who will inform the principal investigator. Parents may also inform the principal investigator directly (contact information is available at the end of the information sheet that goes with the consent form). For, all patients, the speech-language pathologist must send a patient identification form to the principal investigator indicating the date the consent was signed, the date of randomization, the randomization group, and, if applicable, the date of discharge from the trial.

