### Criteria for discontinuing or modifying allocated interventions {11b}

The criteria for discontinuing or modifying allocated interventions are: (a) a serious adverse event (disease or pandemic) or environmental event (relocation), (b) withdrawal of consent, (c) cessation of daily training for more than 15 days without valid reason and subject to the judgment of the investigator, or an irregularity in daily training subject to the judgment of the investigator. Post-intervention measures for children that drop out from the intervention will be taken to perform an intention-to-treat analysis.

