### Plans to promote participant retention and complete follow-up {18b}

The principles of therapeutic education and shared decision making are used to maintain the children’s participation during the 16 months. Participants and their parents receive all the information necessary to understand developmental dyslexia and the protocol of care offered to them. This information is presented and repeated throughout the duration of the study on different media (slide show and fact sheets). Most interventions at home are standardized and computerized. The role of the parents is making sure that the children respect the daily sessions, supporting them by being present during the numerical training and carrying out the verbal trainings such as BlendSeg or ARMAR. The children and their parents are also trained in using the software on their own by means of tutorials. The outcomes obtained during the different phases of the study are communicated very precisely and explained to the parents and children. The child can decide to leave the study at any time. The data collected until the withdrawal of consent or the end of participation is kept and analyzed as specified in the information leaflet given to the parents.

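### Intention-to-treat is misdescribed as an analysis of the children who quit, and the exit criteria conflict with section {11b} on whether poorly adherent children stay in assessment and analysis

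*Protocol article*

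**What the plan says.** - **Abstract, Methods.** After a clause on implementation fidelity, the text says that an intention-to-treat "analysis will be performed on the children who quit the trial before the end".
- **Exclusion criteria (or study exit criteria).** The list opens with "Participants are temporarily or permanently excluded from the study if". One ground is "They interrupt daily training for more than a continuous period of 15 days without a valid reason determined at the investigator’s discretion". Another is "They do not participate regularly in daily training, as left to the investigator’s appreciation". The third is withdrawal of consent. On timing, the section adds: "The interruption may occur after consent has been obtained or after randomization".
- **Section {11b}.** The same two adherence grounds appear, together with serious adverse or environmental events and withdrawn consent, but as reasons to stop or change the intervention. It ends: "Post-intervention measures for children that drop out from the intervention will be taken to perform an intention-to-treat analysis".
- **Section {18b}.** After noting that a child may leave at any time, it says: "The data collected until the withdrawal of consent or the end of participation is kept and analyzed", as set out in the information leaflet.
- **Section {20c}.** Its heading covers non-adherence and missing data; its text provides only for multiple imputation.
- **Section {20a} and Statistical analysis.** A flowchart will report the numbers randomised and the numbers in the final analysis. Gains between tests are then compared without naming a population.
- **Sections {8}, {17b} and {19}.** The associate investigators are the speech-language therapists, the trial is open-label, and the investigators enter the outcome data on the case report forms.

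**The concern.** An intention-to-treat analysis keeps every randomised child in the allocated group, whatever happens to training. An analysis of those who quit is something else. Taken literally, it leaves the main result to those who stayed.

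That would matter less if nobody left because of how they trained. The exit criteria, however, remove children from the study for interrupted or irregular home training. The irregularity ground has no numeric limit and is decided by someone who knows the allocation, treats the child and reports the outcomes. Section {11b} gives the same grounds a different consequence. A therapist reading both cannot tell whether a child who trained irregularly should still be tested.

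Two kinds of result are exposed. The main contrast compares gains within the child, so randomisation gives it no protection against selection. Phonological versus visual-attentional training at T3, and the order comparison at T4, are randomised, but they keep that protection only if no child is removed for post-randomisation behaviour that may differ between programs.

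**Working it through.** **Step 1: the sections side by side.** What happens to a randomised child who trains irregularly in phase 2?

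| Section | Status of the child | Later tests | Place in the analysis |
|---|---|---|---|
| Abstract, Methods | has quit | not stated | a so-called intention-to-treat analysis of quitters |
| Exit criteria | out of the study, temporarily or permanently | not stated; exclusion suggests none | not stated |
| {11b} | out of the intervention | post-intervention measures, visits not named | intention-to-treat |
| {18b} | withdrawn or participation ended | not addressed | data to that point kept and analysed |
| {20c} | not stated | not stated | missing values imputed |

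The conflict lies between the exit criteria and {11b}. The Abstract is a misdescription. Section {18b} is compatible with {11b}, because a child who stops training need not have ended participation.

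**Step 2: when adherence exits can arise.** Under section {8}, phases 1 and 3 have no intensive home training. Exits for poor home training therefore come from phase 2 only.

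**Step 3: effect on the main contrast.** For each child let D = (phase 2 gain) − (phase 1 gain). Let a fraction q be removed, with mean D_r, and let those who stay have mean D_s. Then

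- all randomised: D_all = (1 − q)·D_s + q·D_r
- error if only stayers are analysed: D_s − D_all = q·(D_s − D_r)

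Removing a child takes out that child's phase 1 gain as well as the phase 2 gain. The error is upward only if D_r < D_s, zero if they are equal, and downward if D_r > D_s.

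**Step 4: illustration.** From section {14}: d = 0.70 and a 10% drop-out rate. That section's 55 per group reproduces with a two-sample t-test at two-sided 5% if power is taken as 95% (54.02, rounded up to 55); the power is not stated, so this is an assumption. No figure there is disputed. Assumptions for the illustration: stayers have D_s = 0.70, all of the 10% are adherence exits, none of their later data are used or imputed, and D_r lies between 0 and half of 0.70.

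- D_r = 0: D_all = 0.90 × 0.70 = 0.63; ratio 0.70/0.63 = 1.11
- D_r = 0.35: D_all = 0.63 + 0.10 × 0.35 = 0.665; ratio 0.70/0.665 = 1.05

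The inflation is about 5% to 11%, or 0.035 to 0.07 in d.

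**Step 5: the randomised comparisons.** The same algebra within each arm gives an error in the arm difference of q1·(D_s1 − D_r1) − q2·(D_s2 − D_r2), with D now the gain being compared. It vanishes if the two terms are equal. The document gives no arm-specific exit rates, so no figure can be attached.

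**The case against.** The best defence is that the intent is already visible. Section {11b} commits to measuring drop-outs for intention-to-treat, {20c} adds multiple imputation, and {20a} promises a flowchart and a description of those lost to follow-up. The Abstract's sentence may be loose wording for an analysis that brings the quitters in. Analysis sets are commonly left to a statistical analysis plan, which is not shown. Therapists' judgements also have an objective record behind them, because the software logs the home sessions ({11c}, {19}).

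Much of this stands, and it rules out several stronger readings that a reader might infer:

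- **That the trial will analyse compliers only.** No section says so, and {11b} points the other way.
- **That {18b} discards later data.** It says what is kept, not that nothing later counts.
- **That exclusion raises the phase 2 gain and leaves the comparator untouched.** The contrast is within-child, so a removed child leaves both sides (step 3).
- **That the effect is inflated by 11%, or by 25% with 20% removed (1/0.80 = 1.25).** Both figures assume zero extra gain in every removed child and no use of later measurements or imputation. The 20% has no basis in the document, and the 10% in {14} is drop-out of unspecified cause.
- **That {11b} already foresees tests T3 to T6 for these children.** It names no visits.

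The defence does not remove the wrong description in the Abstract or the contradiction between the exit criteria and {11b}. These are statements in the document, not silences that a later plan would ordinarily fill. Session logs do not supply the missing threshold.

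**Conclusion.** The point holds as a contradiction that should be corrected. The Abstract misdescribes intention-to-treat. The exit criteria and {11b} attach different consequences to the same adherence grounds, and no section makes all randomised children the main analysis set.

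If the Abstract and the exit criteria are followed literally, the main contrast and both randomised comparisons can be selected on phase 2 adherence. For the main contrast the error favours training if poor adherers have a smaller gain difference than the others, which is plausible but not shown. Its size cannot be computed from the document, and the 5% to 11% rests wholly on the assumptions in step 4. Following {11b} and imputing missing tests would reduce the risk, so bias is possible rather than established. Confidence is high on the wording and lower on the consequence.

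**What to change.** 1. State in the Abstract and in the statistical section that the main analysis includes all randomised children in their allocated order.
2. Reword the exit criteria, consistent with {11b}, so that meeting an adherence criterion does not by itself remove a child from assessment or analysis.
3. Take the remaining scheduled tests unless consent is withdrawn, and state in {11b} which visits the post-intervention measures cover.
4. Use the multiple imputation in {20c} only for tests that are truly missing.
5. Limit adherence-based exclusion to a per-protocol sensitivity analysis, with thresholds fixed in advance and applied to the session logs described in {11c} and {19}.

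The rule for stopping training is not at issue and no change to it is proposed; the sections need only be reconciled. The cost is mostly wording, plus a few extra tests on children who stopped training. Because {11b} names no visits, some of these tests may be a new requirement. The estimated effect may also be somewhat smaller.

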**Discussion:**

The main objective of this study is to assess whether the three types of intensive intervention (phase 2) improve reading skills compared to baseline (i.e., non-intensive intervention, phase 1). The secondary objectives are to evaluate the effectiveness of each intervention and to test the effects of order of delivery on reading intervention outcomes. Reading comprehension, spelling performance and reading disorder impact of dyslexic readers are assessed immediately before and after the multimodal intervention and 2 months post-intervention.

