## Objectives {7}

### Main objective

The main objective of this study is to assess whether the combination of three types of intensive interventions (phase 2) improve reading and spelling skills compared to baseline (i.e., non-intensive intervention, phase 1).

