### Secondary objectives

Assess the efficiency of each intervention against baseline.Assess the efficiency of each intervention as a function of the severity of the “underlying cognitive deficits”.Assess the effects of intensive intervention (phase 2) compared to baseline (phase 1) on reading interest, academic performance, and self-esteem.Assess the stability of the intervention effects in all of the above measures 2 months after training.

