### Main hypothesis

Intensive and specific multimodal training significantly improves reading (fluency, comprehension) and spelling skills compared to a conventional non-intensive and non-specific therapy. These effects of intervention will be tracked after the three training phases (test 5) and 2 months later (test 6).

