### Secondary hypotheses

*Hypothesis 1*: Intensive phonological or visual-attentional training is more effective than conventional non-intensive and non-specific therapy*Hypothesis 2*: Intensive, specific, multimodal training (test 5) significantly improves reading interest, academic performance, and self-esteem compared to conventional non-intensive therapy (test 2).*Hypothesis 4*: These intervention benefits should last 2 months later (test 6).*Hypothesis 5*: No significant difference as for the effects on reading skills is expected between phonological versus visual-attentional training (test 3).

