## Interventions

### Explanation for the choice of comparators {6b}

#### Main evaluation criteria

Reading efficiency is measured at inclusion (Test 1), at the end of phase 1 without intensive training (Test 2), at the end of the three training periods of phase 2 (Test 5) and after phase 3, i.e., 2 months after the training has stopped (Test 6) by five reading tests:Alouette©, a widely used standardized French reading test, measures speed and accuracy when reading a meaningless text and provides a reading age [113] and both speed and accuracy scores [114].DeltaText© measures speed and accuracy of meaningless texts matched in number of words, length and complexity [119].Mouette-Pingouin© measures the speed and accuracy of word identification of meaningful texts matched in length and complexity to control for a test/re-test effect using two texts controlled for word number and word frequency [115].Eval2M© measures the speed and accuracy of identification of words presented in columns [115].Evalec© measures the respective speed and accuracy of identification of regular words, irregular words and pseudowords [116].

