#### Assessment of reading disability impact

Changes in reading disability, reading motivation, academic performance and self-esteem are measured by two questionnaires. These questionnaires consist of several statements for which the respondent expresses his or her degree of agreement or disagreement. Two Likert scales are constructed, one for the child, one for the parents, and are proposed before and after training (for more details, see Additional file 8).

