### Statistical analysis

To assess the gains for each dependent variable (reading, spelling and reading comprehension scores) in each group (1 and 2) and for the total sample, we will calculate the means difference and confidence intervals between T1 and T2 (Phase 1 without training), between T2 and T4 (Phase 2 after 16 weeks of training), between T4 and T5 (Phase 2 after 24 weeks of training), and between T5 and T6 (Phase 3 after 8 weeks without training).The gains between T1 and T2 will be compared with the gains between T2 and T4, between T4 and T5, and between T5 and T6 to determine whether the T2T4, T4T5, and T5T6 differences represent a significantly greater gain compared to the no training phase (T1T2).

To measure the effect of each type of training, we will calculate the effect size, *Cohen’s d* or *η*^*2*^, from the gains of each dependent variable. Cohen’s d scores of 0.3, 0.5 and 0.8 are considered to represent small, medium and large effect sizes, respectively.3.To determine whether the order of PHO/VA versus VA/PHO training leads to different effects, we will perform a repeated Anova with cross-over between groups to compare the gains between T2 and T4 of each group, controlling for gains between T2 and T1 without training. This analysis will also allow us to determine if there is a significant difference between the effects of 8 weeks of phonological training and 8 weeks of visual-attentional training between T2 and T3.4.Exploratory factor analysis will verify that all the items in the questionnaires (pre-test and post-test Likert scale) or, failing that, some of them can be combined into a score. If necessary, the composite scores will be analyzed as continuous variables. If not, graphical representations in the form of histograms will be used to visualize the variations, and χ^**2**^ tests will be carried out.

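### The questionnaire objective promises a comparison with Phase 1, but the planned contrast is an uncontrolled change from T2 to T5; for spelling and comprehension the stated visits and the planned gains contradict each other

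*Protocol article*

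**What the plan says.** **Objectives and hypotheses.** One secondary objective is to "Assess the effects of intensive intervention (phase 2) compared to baseline (phase 1) on reading interest, academic performance, and self-esteem". Hypothesis 2 restates it for the training as a whole at test 5, which "significantly improves reading interest, academic performance, and self-esteem compared to conventional non-intensive therapy (test 2"). The Main objective asks whether the three interventions together "improve reading and spelling skills compared to baseline (i.e., non-intensive intervention, phase 1"), and the Main hypothesis covers comprehension as well: "Intensive and specific multimodal training significantly improves reading (fluency, comprehension) and spelling skills compared to a conventional non-intensive and non-specific therapy".

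**Timing.** The abstract says that comprehension, spelling and reading disorder impact "are assessed immediately before and after the multimodal intervention and 2 months post-intervention". On the questionnaires, the section Assessment of reading disability impact says: "Two Likert scales are constructed, one for the child, one for the parents, and are proposed before and after training". The Secondary evaluation criteria name the instruments for spelling (Chronosdictées), comprehension (ORLEC L3) and impact, but give no visits for them. The five reading tests do have stated visits: "Reading efficiency is measured at inclusion (Test 1), at the end of phase 1 without intensive training (Test 2"), then T5 and T6, with T3 and T4 added under the secondary criteria.

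**Analysis.** The Statistical analysis section begins: "To assess the gains for each dependent variable (reading, spelling and reading comprehension scores) in each group (1 and 2"). It plans the gains T1 to T2, T2 to T4, T4 to T5 and T5 to T6, and tests the last three against the first. The questionnaires are not in that list. They have their own paragraph, which describes a pre-test and post-test scale.

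**The concern.** The trial has no untrained control group; the Trial design section explains this on ethical grounds. The control for the question of intensive training against usual therapy is therefore a period within each child: Phase 1, from T1 to T2. An outcome uses that control only if its change over Phase 1 is known, which takes a value at T1 and one at T2.

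For the questionnaires the visible text provides no Phase 1 change, and Hypothesis 2 lets the T2 score stand for conventional therapy. A significant rise from T2 to T5 would then be read as superiority over conventional therapy. The same rise could come from growing older, from a further term of school, from answering the form a second time, or from the expectations of children and parents who know that training has been given.

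For spelling and comprehension the stake is different. Two places in the article imply different visit schedules, and on one of them most of the planned gains cannot be calculated.

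**Working it through.** **Step 1: visits stated against visits needed.**

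- *Questionnaires, stated:* before training (T2), after training (T5) and, in the abstract, two months later (T6). Hypothesis 2 uses T2 and T5.
- *Questionnaires, needed for a Phase 2 against Phase 1 effect:* T1, T2 and T5. T1 is absent from every visible statement of timing. The change T5 − T2 can be calculated, but there is no T2 − T1 to set against it.
- *Spelling and comprehension, stated in the abstract:* T2, T5, T6.
- *Spelling and comprehension, needed by the Statistical analysis section:* T1, T2, T4, T5, T6. T1 and T4 are not in the abstract's list. Read literally, three of the four planned gains (T1 to T2, T2 to T4, T4 to T5) could not be formed; only T5 to T6 could.
- *Evidence for a T1 value:* the Background says that an assessment of reading and spelling sets each child's reading profile, and the Intervention description ties the individual profile to the initial evaluation at Test 1. That implies spelling at T1. For comprehension the only pointer is that the gain analysis presupposes it. Table 1, the visit schedule, is not visible.

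**Step 2: what T5 − T2 estimates.** The interval is three trainings of 8 weeks, 3 × 8 = 24 weeks. Then T5 − T2 = training effect + 24 weeks of ordinary change + retest + expectancy. A T1 to T2 change would estimate 8 weeks of ordinary change and retest under usual therapy. The contrast that uses it is (T5 − T2)/3 − (T2 − T1), both per 8 weeks. Without T1 the second term does not exist.

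**Step 3: illustration of size.** The article gives no drift or correlation, so these are assumptions. The sample-size calculation (55 per group for reading efficiency) plays no part.

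- Children analysed: 120 × (1 − 0.10) = 108, from the Sample size section.
- Assumed ordinary drift: 0.05 to 0.10 SD per 8 weeks, so 0.15 to 0.30 SD over 24 weeks. True training effect: zero.
- SD of change = √(2(1 − r)), in baseline SD units; standardised change = drift / SD of change; two-sided paired t-test at 5%.
- r = 0.6: SD of change = √0.8 = 0.894. Drift 0.15 gives 0.168 and rejection 0.41; drift 0.30 gives 0.335 and rejection 0.93.
- r = 0.8: SD of change = √0.4 = 0.632. Drift 0.15 gives 0.237 and rejection 0.69; drift 0.30 gives 0.474 and rejection above 0.99.

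**The case against.** The strongest reply has four parts.

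*The timing rests on an abstract sentence.* That sentence does not say that these are the only visits, and the schedule in Table 1 and the case report forms are not visible. A reader might infer that spelling, comprehension and the questionnaires all lack a Phase 1 gain. The documents do not support that for spelling or comprehension: a T1 spelling assessment is implied, and the gain analysis presupposes T1 data for both. What remains for these two is a contradiction. For the questionnaires the reply is weaker, because the abstract, the assessment section, the analysis paragraph and Hypothesis 2 agree on measurement before and after training.

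*T2 closes Phase 1, so T5 against T2 is a comparison with baseline.* This is true of the level, and it would be too strong to say that no comparison with baseline is possible. It is not a comparison with the Phase 1 change, and that is what an effect of Phase 2 relative to Phase 1 requires. Nor does the gain analysis ask for a T1 to T2 gain on the questionnaires; the conflict is with the objective.

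*The error rates are assumed.* This stands. The documents give no reason why self-esteem or reading interest should rise with schooling. The Data management section allows percentiles or standard deviations, and age- or grade-normed scores would already remove much ordinary growth. The paired test is also not what is planned for spelling or comprehension.

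*The main criteria are untouched.* This stands too. The five reading tests have explicit T1 and T2 visits, and spelling, comprehension and impact are listed as secondary criteria.

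**Conclusion.** The point holds in two parts of unequal strength.

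For the questionnaires, the objective and the planned contrast do not match. On the visible text the plan would present an uncontrolled, open-label change over 24 weeks as an advantage over conventional therapy. This conclusion rests on the consistent timing statements and would change only if T1 questionnaire scores were in fact collected. Even then, Hypothesis 2 as worded would not use them.

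For spelling and comprehension, the finding is an inconsistency between the abstract (T2, T5, T6) and the Statistical analysis section (which also needs T1 and T4). It is not shown that the Phase 1 gain is missing.

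The rejection rates of 41% to 93% and 69% to over 99% illustrate how far a before-after test can mislead under assumed drift and correlation. They should not be read as the error rate of this trial. The consequence is confined to claims on these outcomes; the main reading outcomes keep their Phase 1 control.

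**What to change.** 1. State the visits for ORLEC L3, Chronosdictées and each questionnaire, and make the abstract, the section on reading disability impact and the Statistical analysis section agree with them.
2. Where T1 values exist, define the test as the T2 to T5 gain per 8 weeks, (T5 − T2)/3, against the T1 to T2 gain.
3. Drop the T2 to T4 and T4 to T5 gains for any outcome not measured at T4.
4. Where T1 values do not exist (on the visible text, the questionnaires), remove from the objective the comparison with Phase 1 and from Hypothesis 2 the comparison with conventional therapy. Report T2 to T5 as an uncontrolled change that supports no efficacy claim.

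The cost is wording and analysis. Recruitment was due to end in September 2021, so adding T1 assessments is unlikely to be possible. It would also have a cost of its own for spelling: Chronosdictées has two dictations per grade level, so more than two administrations may repeat one. The price of the fix is a narrower claim on secondary outcomes.
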